## Abstract

**Background:**

Cognitive impairments, especially deficits of executive function, have been well documented as a core and early feature in Huntington’s disease (HD). Cognitive impairments represent considerable burden and can be devastating for people and families affected by HD. Computerised cognitive training interventions that focus on improving executive function present a possible non-pharmacological treatment option. We propose to determine the feasibility, acceptability, and appropriate outcome measures for use in a randomised controlled feasibility study.

**Methods/design:**

Participants will be randomised into either a computerised cognitive training group or a control group. Those randomised to the training group will be asked to complete a cognitive training intervention based on the HappyNeuron Pro software tasks of executive function, for a minimum of 30 min, three times a week for the 12-week study duration. Participants in the control group will not receive computerised cognitive training but will receive a similar degree of social interaction via equivalent study and home visits. We will explore quantitative outcome measures, including measures of cognitive performance, motor function, questionnaires and semi-structured interviews, as well as magnetic resonance imaging (MRI) measures in a subset of participants. Feasibility will be determined through assessment of recruitment, retention, adherence and acceptability of the intervention.

**Discussion:**

The results of this study will provide crucial guidance and information regarding the feasibility of conducting a randomised controlled study into computerised cognitive training in HD. This study is crucial for the development of larger definitive randomised controlled trials which are powered to determine efficacy and for the development of future cognitive training programmes for people affected by HD.

**Trial registration:**

The study is registered on clinicaltrials.gov and has the unique identifier NCT02990676.

## Background

### Background and rationale

Huntington’s disease (HD) is caused by a CAG repeat trinucleotide expansion within the first exon of the *huntingtin* gene [1], and it causes a range of symptoms including motor, cognitive and psychiatric disturbances [2–8]. These disease symptoms significantly affect daily activities, independence and quality of life, even during the early stages of the disease [9, 10]. Cognitive dysfunctions early in the HD disease process have been well documented and can include specific problems with attention, cognitive flexibility and memory [11, 12]. Therefore, cognitive training interventions, which focus on tasks that require executive function, present a potentially exciting non-pharmacological treatment option for neurodegenerative diseases including HD. Studies in HD mice have previously demonstrated executive function impairments [13, 14], and subsequent studies have shown that cognitive training can benefit HD mice and modify the associated cognitive and motor disease symptoms [15, 16]. These results provide important ‘proof of principle’ evidence that an early cognitive training intervention may be beneficial in HD.

Furthermore, there is accumulating evidence in both healthy and clinical populations that cognitive training, via repeatedly conducting tasks that require specific aspects of executive function such as attention, reasoning, dual tasking and memory, can improve cognitive functions in the trained domain [17–20]. For instance, computerised cognitive training on such tasks has been found to improve cognitive impairments in Alzheimer’s disease [21–23] and Parkinson’s disease [24–26]. In addition, a recent single arm feasibility study demonstrated the feasibility of and adherence to working memory training on the Cogmed QM programme in a small sample of HD patients [27]. Furthermore, previous studies have found that training-related changes are associated with alterations in white matter, particularly with regard to altered myelination in both healthy controls [28] and HD [20]. Thus, we intend to use MRI measures to explore the potential neural mechanisms which may be associated with computerised cognitive training in the HD clinical population.

The utilisation of computerised cognitive training strategies may provide several advantages over repeating practical tasks [17, 18]. Computerised cognitive training strategies are automated and often provide adaptive difficulty levels based on participant performance. Furthermore, they can be completed by participants at their convenience, they provide automated tasks which require comparatively little demand on motor function and they provide several objective outcome measures which can be used to detect subtle changes in function [21–26]. Furthermore, the HappyNeuron cognitive training software, that we intend to use in this study, can be made available in different languages to allow for consistent training globally, and it provides an interface for the researcher to observe the progress of participants.

Despite this, computerised cognitive training interventions are yet to be extensively investigated in the HD clinical population. Therefore, this feasibility study will clarify key uncertainties regarding the study design, participant eligibility and willingness of potential participants to consent to the study and be randomised as well as recruitment, retention and acceptability. It will also facilitate the evaluation of outcome measures and an estimation of effect of the intervention. This study is a necessary step before proceeding to a fully powered efficacy trial in the HD patient population [29].

### Aims and objectives

The primary aim of this study is to determine if computerised cognitive training is feasible and acceptable for people with HD in the setting of a randomised controlled study. A secondary aim is the exploration of outcome measures of cognitive function, motor function and questionnaires. Furthermore, we will explore possible mechanistic measures of training-related plasticity through magnetic resonance imaging (MRI) metrics.

#### Primary objective

(i)To assess the feasibility of delivering a home-based computerised cognitive training programme for people with HD, utilising both quantitative and qualitative measures considering:
- The willingness of eligible participants to receive the intervention and participate in a randomised controlled study- Potential barriers to recruitment- Potential barriers to completion of the study- Response rates and adherence to the computerised cognitive training programme

#### Secondary objectives

(i)To explore group effect estimates between the cognitive training intervention group in comparison to the control group.(ii)To use MRI techniques in a subset of participants to explore the potential neural mechanisms of brain plasticity that may underpin any observed effects.(iii)To evaluate the intervention using participant and family member/carer feedback to inform future trials in this patient population.

### Study design

The proposed study is a randomised feasibility study of an online computerised cognitive training intervention for people with HD, to be completed in the home. Those allocated to the control group will be asked to continue as normal. All participants will receive home visits. The home visits will include a battery of cognitive tests for both groups; those allocated to the intervention will receive support in setting up the computerised cognitive training software. Within the overall study, a subgroup of 16 participants will undergo MRI at baseline, and approximately 6 weeks into the intervention, MRI will be offered to participants on a first come first served basis for those who are eligible and willing. The feasibility of repeated imaging in this patient population will be ascertained, and an exploration of the most appropriate MRI metrics will also be undertaken as part of the feasibility study.

The study schema is illustrated in Fig. 1.

**Fig. 1 Fig1:**
[figure not shown]
Schematic representation of feasibility study

## Methods

### Participants, interventions and outcomes

#### Study setting

Participants will be recruited from the Cardiff HD Centre at Cardiff University. Study assessments will take place in the Hadyn Ellis Building (HEB) and Cardiff University Brain Research Imaging Centre (CUBRIC). Many patients attending the centre are already participating in the Enroll-HD observational study (REC no. 04/WSE05/89), which longitudinally monitors the progression of disease symptoms. Enroll-HD participants provide permission to be contacted about other HD research studies and for their coded data to be accessed by researchers conducting HD-related research; therefore, these participants will be approached for this study. As such, a full clinical data set including full medical and medication history will be available for each research participant. In addition, we will seek consent to approach participant family members, friends and carers for interview, although involvement of a family member, friend or carer is not a requirement for participation in the study.

#### Eligibility criteria

Inclusion and exclusion criteria for the study are shown in Table 1. The inclusion and exclusion criteria are broad to determine feasibility for a range of disease stages which will inform the design and delivery of future trials.

**Table 1 Tab1:** Inclusion and exclusion criteria

Inclusion criteria	Exclusion criteria
• Confirmed HD diagnosis by genetic test. • Over 18 years of age. • Enrolled in the Enroll-HD study. • Stable medication regime 4 weeks prior to recruitment (and not anticipated to change medications during the study period).	• Inability to provide consent. • Any known neurological condition (other than HD). • Currently actively involved in any other interventional trial (i.e. have begun the intervention) or within 4 weeks of completing the final assessments of an interventional trial. • Currently regularly completing a computerised cognitive training intervention. • For the subset of participant’s eligible and willing to have an MRI scan, MRI contraindications (e.g. a pacemaker) as established using CUBRIC’s standard screening procedures*.* In addition, significant levels of disease-related chorea will exclude participants from MRI.

#### The cognitive training intervention

The 12-week cognitive training intervention, using HappyNeuron Pro software, will be completed in participant homes. The software is automated, such that it provides non-biased data recording and an interface which allows the researcher to track compliance remotely. It has previously been validated in both healthy controls [30] and patients with depression [31] and has shown patient benefit including improved cognition and functionality.

The cognitive training intervention will comprise six tasks developed by HappyNeuron which are specifically aimed at training within the executive function domain.

These tasks include:‘Writing in the stars’

The participant is given a list of nine words. Only six of them can be used to fill the empty squares and connect with each other to form the six-point star. This exercise aims to train logical reasoning in order to determine which six words to choose from the list of nine, to find which positions of letters are common to two or three words.2.‘Basketball in New York’

The participant sees a first line of three hoops with coloured basketballs inside. In the second line, they will have to determine the number of basketball moves that are required to reach the same configuration as the first line of hoops. This exercise aims to train visual mental imagery as all the possible actions must be visualised in order to complete the task.3.‘Decipher’

The participant is asked to decipher quotations where the letters have been replaced, either by letters or by symbols. Each letter is always replaced by the same letter or symbol. This exercise is designed to train the participant’s concentration, language (spelling, grammar rules, letter frequency), logic and the capacity to make deductions from hypotheses.4.‘The Towers of Hanoi’

The participant must configure coloured rings on a series of pegs to match a target image. There are a number of rules. The participant can only move one ring at a time and can never put a larger ring on top of a smaller ring. This task is designed to train temporal-spatial design, memory and planning skills. This computerised task is directly related to the ‘real life’ version which will be completed during the participant home visits; thus, we will investigate any possible transfer effects of this training.5.‘Hurray for change’

This task comprises two exercises. In the first part, a series of 4 to 16 letters or words must be linked in alphabetical order. The second part demands that the participant alternately sorts two series of items. This exercise requires concentration and visual and spatial exploration skills. It is designed to train mental flexibility, visual and verbal working memory and language skills. This online task is similar in nature to the trail making tasks which are included as part of the written study assessments. Thus, we will analyse any transfer effects.6.‘The right count’

In this exercise, the participant is presented with a series of numbers and mathematical symbols to perform mental arithmetic calculations. This game trains working memory, executive function (calculation and arithmetic reasoning) and mental imagery.

The tasks have an adaptive design in that when completing the tasks, participants are required to achieve an 80% level of accuracy twice within the testing period in order to progress to the next level of the task. If a participant achieves less than 60% accuracy on a task, they will be automatically moved to a lower difficulty level. There is a maximum of nine difficulty levels in each task available to participants. If a participant reaches level nine, they will be required to continue at this level for the remainder of the training. Performance data is recorded at the completion of each game and is transmitted and stored on the HappyNeuron server.

Participants will be asked to complete the HappyNeuron Pro training for a minimum of 30 min three times a week for 12 weeks, based on the recommendations of the software provider. Completion of the cognitive training programme will be supported by email or telephone reminders and remotely monitored by the researchers through an interface. The data generated during the intervention, including the tasks completed, duration of tasks and levels achieved will be stored according to HappyNeuron policies and exported to the researchers upon request.

Participants allocated to the control group will be asked to continue as normal for the 12-week duration. The control participants will also receive home visits, to control for increased social interaction.

#### Involvement of nominated carers, friends or family members

The intervention is designed to be completed independently by the participant. However, as part of this feasibility study, we will be investigating if any nominated carers, family members or friends help or aid any of the participants in completing the intervention. Participants and nominated carers, friends or family members will be instructed that they may help the participant if they feel able and willing, although they are not specifically required to do so. However, they must not complete the training for the participant. The involvement of carers, family members or friends may be an important aspect of the study and something that will be specifically explored in the semi-structured interviews in order to inform future trials.

#### Outcome assessments

As this feasibility study is exploratory in nature, the outcome measures selected for inclusion in this study will be utilised to inform future larger trials. Baseline and outcome assessments will be completed during the study (Table 2), in addition to MRI measures which will be completed at baseline and 6 weeks into the intervention. An extended battery of cognitive assessments will be completed during home visits (Table 2).

**Table 2 Tab2:**
[figure not shown]
Study outcome assessments

Overall assessment categories are indicated in shaded boxes

*Tests to be included in the extended battery of cognitive assessments to be completed in participant homes during study home visits

#### Participant timeline

The participant timeline is shown in Table 3.

**Table 3 Tab3:**
[figure not shown]
Schema of assessments and intervention

Shaded areas indicate subgroups of study assessments

#### Withdrawal and loss to follow-up

If a participant wishes to withdraw from the study, they can inform the researchers conducting the study or any member of the research team at any time, in person, via telephone or in writing. If a participant initially consents but subsequently withdraws from the study, a clear distinction will be made as to what aspect of the study the participant is withdrawing from utilising a study withdrawal form.

#### Sample size

This is an exploratory feasibility study which aims to establish the feasibility of conducting a randomised controlled study into computerised cognitive training intervention in the HD patient population and provide evidence for a formal power calculation. We will aim to recruit 50 participants with a target of randomising 40 participants. The suggested numbers are based on previous literature regarding cognitive training in other diseases [21–27]. A subgroup of 16 participants (*n* = 8 in the training and *n* = 8 in the control group) will undergo MRI scanning before and 6 weeks into the intervention.

#### Recruitment

An invitation letter and information sheet will be sent to potential participants who are already participating in the Enroll-HD study. In addition, Enroll-HD participants may be approached during their clinical visits and will be informed of the study. Potential participants will be given sufficient time to ask questions, discuss the study with the researchers and discuss the study further with their family and friends. Potential participants who wish to participate will be reminded that they can change their mind or withdraw without reason at any time and that their decision will not affect the standard care that they receive. Willing participants will be asked to sign a consent form, and the initial assessments will then begin.

All potential participants will be screened for their eligibility based on the inclusion/exclusion criteria. MRI scanning is an additional component of the study for those who are eligible. Thus, as part of the screening process, eligible participants will be screened for contraindications to MRI and will be asked to sign an additional consent form which ensures that they understand the potential risks of MRI.

### Assignment of interventions

#### Sequence generation, allocation concealment mechanism and implementation

Randomisation will be performed using a minimisation procedure utilising Minim computer software [32] to ensure balance between the groups for categorical variables of age and cognitive function (determined by the categorical verbal fluency test). Age and cognitive function were chosen as balancing variables, as they have been shown to be significantly associated with cognitive ability [33, 34]; thus, they will be given the same weighting during the minimisation procedure. Allocation and the minimization procedure will be performed by an independent statistician who will input the balancing variables into the Minim software in order to provide the group allocation (intervention or control) for each research participant.

#### Blinding (masking)

Blinding is not used in this study, due to limited resources and staffing. Participants allocated to the intervention group will know that they have been allocated to this group as they are required to complete the cognitive training intervention. The lack of blinding is a limitation of the study design; however, quantitative outcome measures have been utilised where possible in order to minimise the possible bias that may be introduced due to a lack of blinding.

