#### MRI analysis

Potential cognitive training-related changes in the microstructure of white matter pathways of the basal ganglia and motor systems will be assessed with quantitative metrics based on diffusion-weighted (fractional anisotropy, mean and radial diffusivity) and magnetization transfer-weighted MRI (macromolecular proton fraction as proxy MRI metric of axon myelin) [35–37]. Changes in basal ganglia volume will be investigated by extracting subcortical volumes with the FSL-FIRST pipeline [38]. Changes in cerebral blood flow will also be investigated across the whole brain as well as subcortical basal ganglia regions using established methods [39]. The quantitative metrics of tissue structure and blood flow will be correlated with changes in cognition to investigate training-related brain-function associations as well as measures of disease severity, including CAG repeat length, disease burden and Unified Huntington’s Disease Rating Scale (UHDRS) motor scores, using data previously collected and stored as part of the Enroll-HD study.

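### Blinding is dropped at every step for lack of staff, but that reason does not cover off-line MRI processing or the group comparison, and quantitative scoring is not in itself a safeguard

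*Protocol article*

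**What the plan says.** The section Blinding (masking) is categorical: "Blinding is not used in this study, due to limited resources and staffing". It adds that "Participants allocated to the intervention group will know that they have been allocated to this group", since they do the training. It concedes that "The lack of blinding is a limitation of the study design", and then gives one mitigation: "quantitative outcome measures have been utilised where possible in order to minimise the possible bias".

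The abstract lists the outcomes as "measures of cognitive performance, motor function, questionnaires and semi-structured interviews, as well as magnetic resonance imaging (MRI) measures in a subset". Under Study design, home visits include cognitive testing in both groups, while "those allocated to the intervention will receive support in setting up the computerised cognitive training software". Under Data collection methods, MRI data are stored and then downloaded for processing and analysis. Under MRI analysis, one of several metrics is described thus: "Changes in basal ganglia volume will be investigated by extracting subcortical volumes with the FSL-FIRST pipeline". Confidentiality gives every participant a study number. The section on sequence generation says "Allocation and the minimization procedure will be performed by an independent statistician".

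Group effect estimates and MRI mechanisms are the first two secondary objectives. Sample size and Discussion say that the data will support a later power calculation.

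**The concern.** One reason, shortage of staff, is used to drop masking everywhere. It fits the people who meet participants. It does not obviously fit work done on files after the visit, where masking is a matter of labelling. Because the statement is categorical and no masked step appears elsewhere in the article, a fuller protocol could add one only by contradicting it.

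The mitigation also promises more than it can deliver. Quantitative describes the form of a score, not its independence from whoever gives or completes the test. A reader could take open-label questionnaire and performance scores to be protected when they are not.

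At stake are the exploratory group differences and MRI changes. They will help to choose outcomes and set the sample size of a definitive trial, so bias that could have been avoided here is carried into that planning.

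**Working it through.** **Which steps does the staffing reason cover?**

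| Step | What the article shows | Does the staffing reason explain no masking? |
|---|---|---|
| Participants | They do the training, or do not | Not needed; masking is impossible in any case |
| Visit assessment | Software support goes to the training arm only (Study design) | Yes; whoever runs the visit is likely to learn the arm |
| Scoring of paper tests | Written tests and paper forms; the scorer is not named | Possibly; a masked scorer might be a second person |
| MRI processing | Downloaded, processed off-line, one pipeline named | Not explained |
| Group comparison | Study numbers exist; an independent statistician allocates | Not explained |

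The point rests on the last two rows.

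**How precise are the estimates concerned?** The article states no alpha, power, effect size or SD, so there is no planned figure to reproduce. The inputs are 40 to be randomised and 8 + 8 scanned (Sample size). I assume equal arms of 20 and no dropout. In SD units, SE = sqrt(2 / n per arm).

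- 20 per arm: sqrt(2/20) = 0.316; 95% half-width 1.96 × 0.316 = 0.62.
- 8 per arm (MRI): sqrt(2/8) = 0.50; 95% half-width 1.96 × 0.50 = 0.98.

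**How would a bias compare?** The document gives no bias. Over an assumed range of 0.1 to 0.4 SD:

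- 20 per arm: 0.1/0.316 = 0.3 SE to 0.4/0.316 = 1.3 SE.
- 8 per arm: 0.1/0.50 = 0.2 SE to 0.4/0.50 = 0.8 SE.

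A bias in this range lies inside the 95% half-width in both cases, so the data would not reveal it.

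**What could follow for the next trial?** This is an illustration only, on assumed true effects and assumed total bias from unmasked assessment. With two-sided 5% and 80% power, n per arm = 2(1.96 + 0.84)² / d². True power is that of the resulting n at the true effect.

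| True effect (SD) | Assumed bias (SD) | n per arm planned | True power |
|---|---|---|---|
| 0.3 | 0 | 175 | 80% |
| 0.3 | 0.1 | 99 | 56% |
| 0.3 | 0.2 | 63 | 39% |
| 0.5 | 0 | 63 | 80% |
| 0.5 | 0.1 | 44 | 65% |
| 0.5 | 0.2 | 33 | 53% |

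These figures show how sensitive planning is to an inflated estimate. They do not measure what masking the desk steps would save, because those steps contribute only part of any total bias.

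**The case against.** The article is candid: it names the lack of blinding as a limitation and says that quantitative measures are used where possible to reduce bias, not that they remove it. Preferring a measured score to an impression is a reasonable partial step, and the full outcome table is not legible here, so how far each outcome depends on an examiner cannot be judged. Automated extraction of volumes leaves little room for knowledge of arm to act. The primary aim is feasibility, the only numerical feasibility threshold is for retention, and training is logged by software. All of this stands, and it limits the weight of the point.

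It does not remove the point. The MRI section covers several metrics and regions, and choices among them can be made with the arm known. Admitting a limitation does not explain keeping the part of it that could be avoided.

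A reader might go further and infer that masking would need no extra staff anywhere, including for paper-test scoring. The document does not support that: it gives no staffing figures and does not say who scores, enters data, processes scans or runs the comparison. A reader might also infer that the independent statistician already holds a concealed key; the article says only that this person performs the allocation. Nor do study numbers alone mask staff who know which participant is training.

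**Conclusion.** The point holds as an inexpensive improvement to a secondary part of the study. The reason given for dropping all masking does not account for unmasked MRI processing or an unmasked group comparison, and the mitigation is overclaimed rather than plainly wrong.

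The gain is confined to the exploratory effect and MRI estimates, and its size cannot be derived from the document. The standard errors of 0.32 and 0.50 SD follow from the planned numbers, given equal arms and full follow-up; the 0.1 to 0.4 SD bias and the power figures rest on assumptions. A reader might take those figures as evidence that the estimates will be biased by that much, or that desk masking would recover that much power. Neither follows. Bias from how tests are given, and from participants knowing their arm, would remain after the change.

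**What to change.** 1. Process and quality-check MRI under newly recoded scan IDs, not the study numbers, with arm and time point hidden.
2. Run the exploratory group comparison on arms coded A and B. Keep training-log data out of that data set, because they exist for the training arm only and would reveal the code.
3. Have the independent statistician keep the key until MRI processing is finished and the analysis data set is locked.
4. Amend the blinding section to say that visit assessments and questionnaires are open-label, and that quantitative scoring limits this bias but does not remove it. If either desk step cannot be masked, say who performs it and why.

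Masked scoring of paper tests is not asked for, since it may need a second person and would not touch bias in test administration.

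The cost is recoding of files, key-keeping added to an existing role, and a paragraph of text. No visit or procedure changes.
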